### 2.3. Mortality Follow-Up

Information on deaths occurring in the study sample during follow-up will be collected by conducting regular mortality follow-ups. The death certificates will be provided by the local health authorities, and the causes of death will be determined according to the International Classification of Diseases (ICD)-10 (WHO).

## 3. Statistical Analysis

Baseline characteristics will be presented as mean ± standard deviation (SD) or as a median and interquartile range for continuous variables; categorical variables will be given as percentages. Patient groups will be compared by Chi-squared test or Fisher’s exact test in case of categorical variables and by *t*-test for in case of continuous variables.

Differences between three or more patient subgroups will be conducted through log-linear models and analysis of variance, and if there are differences, they will be identified using post-hoc-tests.

Cox-Regressions will be carried out for the identification of risk factors and determinants which are related to the binary study outcomes. Confounder-adjusted models will be calculated to estimate relative risks. If age and sex are effect modifiers will be examined. Linear regressions will be applied in case of continuous outcomes if the model assumptions are fulfilled.

An alpha level of 0.05 will be considered significant within the multivariable analyses. In case of multiple testing, the significance level alpha will be corrected. The statistical analysis will be carried out using SAS software, SAS Institute, Cary, NC, USA and R project version 3.5.3, Vienna, Austria.

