## Abstract

Introduction: In Germany, stroke is the third leading cause of death, with more than 60,000 fatalities out of approximately 260,000 cases (first-ever and recurrent strokes) each year. So far, there are only a few long-term studies investigating determinants of the natural course of the disease, especially in the era of mechanical thrombectomy. Materials and Methods: The prospective single-center stroke cohort Augsburg (SCHANA) study will include about 1000 patients treated for stroke in the University Hospital of Augsburg. Patients aged 18 years or older with a confirmed diagnosis of ischemic or hemorrhagic stroke are included in the study. Information on demographic characteristics, onset of symptoms, etiologic factors, comorbidities, quality of life, invasive and non-invasive treatment, complications, and laboratory parameters are collected during a personal interview conducted during the patients’ hospital stay and via a medical chart review. About 30 mL of blood is collected from each patient, and after processing and aliquoting, all blood specimens are frozen at −80° C. The study participants will be followed-up via postal questionnaires at three and 12 months after discharge from the hospital. Furthermore, mortality follow-ups will be conducted. Cox-regression analysis will be used to estimate relative risks. Conclusion: The SCHANA study will generate comprehensive data on the long-term course of the disease. In addition to the main outcomes, recurrent events and survival, patient-oriented outcomes such as health-related quality of life and depression are the focus of the study.

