### 1.1. Primary Outcome

To estimate the impact of thrombolysis, mechanical thrombectomy and drug treatment, comorbidity, treatment-related complications on stroke-related long-term survival, and to examine the frequency and time point of recurrent events; to examine interaction effects between thrombolysis, mechanical thrombectomy and drug treatment on the outcome.

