### 1.2. Secondary Outcomes

To identify factors which are associated with the natural course of the disease.To identify subgroups of stroke patients (by clinical, physiologic, or psychologic features) and to assess optimal in-hospital and outpatient treatment for these subgroups.To explore the requirements of bridging therapy (thrombolysis and mechanical thrombectomy).To evaluate the long-term health-related quality of life and the presence of emotional problems, anxiety and/or depression in stroke patients.To measure and monitor the safety and harm associated with the use of thrombolysis, mechanical thrombectomy, and drug treatments in hospital and after discharge.To investigate the role of blood biomarkers (e.g., inflammatory parameters, adipokines) and of “omics” information (genome, metabolome, and proteome data) in disease development, progression, and outcomes.To determine the health care utilization of patients with stroke, and to determine differences in health care utilization according to age, gender, socio-economic status, and place of residence (urban vs. rural).

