### 2.2. Follow-Up of the Stroke Patients

#### Morbidity Follow-Up and Update of Treatment, Lifestyle and Health Factors

Three and 12 months after hospital discharge, all study participants will receive postal questionnaires or telephone interviews. The postal questionnaires will include questions on disease symptoms, complications, disabilities and comorbidities; behavioral and clinical risk factors (smoking, alcohol consumption, body weight, height); physical activity (German-PAQ-50+) [18]; health-related quality of life (Stroke Impact Scale) [19,20,21] and EQ-5D [22,23]; fatigue and headache (Rostock Headache Questionnaire) [24]; vertigo and depression (PHQ-9) [25,26]; recurrent events, bleeding outcomes, and healthcare utilization (readmissions, visits to physicians, clinics, and emergency departments); and data on current medication. An overview of the data collected at baseline and follow-up is given in Table 1, and a study flow-chart with enrollment and follow-up is depicted in Figure 1.

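### Cox regression is assigned to every binary outcome and reported as a relative risk, which does not fit secondary outcomes read as yes/no states at 3 and 12 months

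*Protocol article*

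**What the plan says.** Section 3 (Statistical Analysis) of the protocol article assigns regression models by outcome type. For binary outcomes: "Cox-Regressions will be carried out for the identification of risk factors and determinants which are related to the binary study outcomes". The effect measure follows: "Confounder-adjusted models will be calculated to estimate relative risks". The Abstract says the same: "Cox-regression analysis will be used to estimate relative risks". For the other outcome type: "Linear regressions will be applied in case of continuous outcomes if the model assumptions are fulfilled". Log-linear models are named only for comparing three or more subgroups. No logistic, log-binomial or Poisson regression is named, nor a constant-time Cox model with robust variance.

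The outcomes are of two kinds. Section 1.1 (Primary Outcome) concerns stroke-related long-term survival and aims "to examine the frequency and time point of recurrent events". Section 1.2 (Secondary Outcomes) includes "the presence of emotional problems, anxiety and/or depression in stroke patients". The follow-up section says how such outcomes are collected: "Three and 12 months after hospital discharge, all study participants will receive postal questionnaires or telephone interviews". The questionnaires cover depression, fatigue, headache, vertigo and disabilities, among other items.

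**The concern.** Cox regression models the time to an event. Depression, fatigue or vertigo reported on a questionnaire is a state on the day of the contact, and the day it began is not what is measured. The rule in Section 3 is not limited to outcomes with an event time, and the only alternative it gives by outcome type is for continuous outcomes. Read as written, an adjusted analysis of a yes/no state at 3 or 12 months goes into a Cox model.

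With every patient given the same follow-up time, all events are tied. The standard tie methods then estimate different things, and none gives the risk ratio together with its correct model-based standard error. At stake are the width of the confidence interval, or the size of the effect itself, for secondary outcomes. The Abstract names depression as one of the patient-oriented outcomes on which the study focuses.

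**Working it through.** **1. The plan's own figure.** Section 4 (Sample Size Estimation) uses a hazard ratio of 1.7, covariate variance 0.36, rho² = 0.3, one-year recurrence of 11%, 80% power and 5% significance (two-sided assumed).

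- Events: D = (1.960 + 0.842)² / (0.36 × (ln 1.7)² × (1 − 0.3)) = 110.6.
- Patients: 110.6 / 0.11 = 1,006, within 1% of the stated 997.

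The calculation therefore rests on time to recurrence and a hazard ratio, where Cox regression fits.

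**2. Hazard ratio called a relative risk, for recurrence.** If 11% is the reference-group risk, the other group has 1 − 0.89^1.7 = 18.0%, a risk ratio of 1.63. If 11% is the overall risk with equal groups, the risks are 8.3% and 13.7%, a ratio of 1.65. Against 1.7 the difference is small.

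**3. A yes/no state at a fixed time.** Assumptions: two groups of n = 400, true risk ratio 1.40, every patient at the same time, model-based variance. The 11% is borrowed from Section 4; reference risks of 20%, 30% and 40% are assumptions, since the article gives none for these outcomes. Write a and c for the events in the two groups, with risks p1 and p0.

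- Breslow ties: the estimate is p1/p0, with SE(log) = √(1/a + 1/c).
- Correct binomial SE(log) = √((1 − p1)/a + (1 − p0)/c).
- Efron ties: the value of b that maximises a·b − Σ ln[n·e^b + n − (l/D)(a·e^b + c)], summed over l = 0 to D − 1, with D = a + c.

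Example, 30% against 42%: a = 168, c = 120. Breslow SE = √(1/168 + 1/120) = 0.1195. Correct SE = √(0.58/168 + 0.70/120) = 0.0964. The ratio is 1.24, and 1 − 1/1.24² = 0.35, so precision falls as if 35% of patients had been discarded.

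| Risks | Breslow estimate | Breslow SE | Correct SE | SE ratio | Efron estimate |
|---|---|---|---|---|---|
| 11% vs 15.4% | 1.40 | 0.197 | 0.184 | 1.07 | 1.43 |
| 20% vs 28% | 1.40 | 0.146 | 0.128 | 1.14 | 1.47 |
| 30% vs 42% | 1.40 | 0.120 | 0.096 | 1.24 | 1.52 |
| 40% vs 56% | 1.40 | 0.104 | 0.076 | 1.37 | 1.58 |

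In the first row the expected count 400 × 0.154 = 61.6 is not whole, so the Efron value was solved with 77 and 55 events in groups of 500, which are the same risks. A third option, discrete ties, returns the odds ratio: (0.42/0.58)/(0.30/0.70) = 1.69 in the third row.

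**4. Check by simulation.** In 600 data sets with 500 per group and risks of 30% and 45% (true ratio 1.50), Breslow ties averaged 1.51, and nominal 95% intervals covered the truth 98% of the time. Efron ties averaged 1.67, with 82% coverage. At 11% and 18.7% (true ratio 1.70), Efron averaged 1.78 with 96% coverage.

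**The case against.** The strongest reply is that the main outcomes are survival and recurrence, that these are a natural reading of binary outcomes in Section 3, and that Cox regression is right for them. This stands, and it removes any effect on the primary aim or the sample size.

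Second, the PHQ-9, the Stroke Impact Scale and the EQ-5D are scored instruments, and scores kept continuous go to linear regression. No cut-off is given. This also stands: the problem arises only for outcomes analysed as yes/no. It does not remove the point, because Section 1.2 words one aim as the presence of a condition, and headache and vertigo are readily analysed the same way. Chi-squared or Fisher tests cover unadjusted comparisons, but not adjusted models.

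Third, a constant-time Cox model with Breslow ties and robust variance would give a valid risk ratio. The text does not exclude it, but does not plan it either.

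Fourth, an article may leave outcome-by-outcome models to a fuller document. Here, however, the article states a rule, and the rule as worded covers outcomes it does not fit.

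A reader might also infer from "The statistical analysis will be carried out using SAS software, SAS Institute, Cary, NC, USA and R project version 3.5.3, Vienna, Austria" that the same data would give different relative risks in the two packages. The documents do not support that. They only list the software; they give no tie method or default setting and do not say that one model will be run in both.

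**Conclusion.** The point holds for adjusted analyses of secondary outcomes treated as yes/no states at 3 and 12 months, and no further. For these, a constant-time Cox model with model-based variance gives either a standard error that is too large (Breslow, by 7% to 37% over reference risks of 11% to 40%) or a risk ratio that is too high (Efron, 1.43 to 1.58 for a true 1.40). Near 11% the error is small; from about 20% upward it becomes material. These sizes rest on the assumed risks, a true ratio of 1.40, equal groups of 400, a common time for all patients and no robust variance.

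Two stronger readings are not supported. One is that the study's main results would be wrong: survival, dated recurrence and the 997 are unaffected, and calling the hazard ratio for recurrence a relative risk changes little at 11% (1.7 against 1.63 to 1.65). The other is that Efron ties estimate exactly the ratio of −ln(1 − risk): they only come close to it. At 40% against 56% that ratio is ln 0.44 / ln 0.60 = 1.61, against 1.58 from the Efron likelihood.

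This should be fixed before analysis, but it does not put the study's main conclusions at risk.

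**What to change.** In Section 3, replace the rule for binary outcomes with two sentences:

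- Cox regression is used for outcomes with an event time (death, dated recurrence), and results are reported as hazard ratios.
- Yes/no outcomes at 3 and 12 months are analysed by log-binomial regression or Poisson regression with robust variance, reported as risk ratios, or by logistic regression, reported as odds ratios.

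One of these models should be chosen in advance, and the Abstract's wording aligned. The methods are standard procedures in the named software. No new data are needed and the sample size does not change.

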## 4. Sample Size Estimation

At the University Hospital of Augsburg yearly, about 1500 patients with acute stroke are treated. Expecting a study participation of about 70% it can be assumed, that altogether about 900 to 1000 patients will be recruited within one year. Based on a previous meta-analysis [27], a cumulative risk of stroke recurrence of 11% within one year can be expected. With an estimated hazard ratio (HR) of 1.7 for the covariate of interest, a variance of 0.36 and a rho^2^ = 0.3, at least 997 patients have to be included to find significant differences with a statistical power of 80% (significance level 5%).

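### The only stated power (80% with 997 patients) uses a covariate variance of 0.36, which a yes/no exposure cannot have, so it does not apply to thrombolysis or mechanical thrombectomy

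*Protocol article*

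**What the plan says.** Protocol article, section 4 (Sample Size Estimation), takes its event rate from a meta-analysis: "a cumulative risk of stroke recurrence of 11% within one year can be expected". It then sets the effect and the covariate inputs, "With an estimated hazard ratio (HR) of 1.7 for the covariate of interest, a variance of 0.36" with a rho² of 0.3, and concludes that "at least 997 patients have to be included" for 80% power at the 5% level. It does not say which covariate is meant, on what scale it is measured, or whether it is continuous or binary. Expected recruitment is "altogether about 900 to 1000 patients will be recruited within one year".

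Section 1.1 (Primary Outcome) puts treatments first among the exposures: "To estimate the impact of thrombolysis, mechanical thrombectomy and drug treatment, comorbidity, treatment-related complications on stroke-related long-term survival". The same section adds the frequency and timing of recurrent events, and interactions between the treatments. Section 3 (Statistical Analysis) names the model: "Cox-Regressions will be carried out for the identification of risk factors and determinants which are related to the binary study outcomes", with adjustment for confounders. The article gives no other power statement.

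**The concern.** In the usual Cox sample size formula, the variance of the covariate drives the result as directly as the event rate does. Thrombolysis and mechanical thrombectomy are procedures that a patient either received or did not. Coded 0/1, such a variable has variance p(1−p), where p is the share exposed. This peaks at 0.25 when half the patients are exposed and falls as exposure becomes rarer. A value of 0.36 lies outside that range.

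The only power figure in the article is therefore one that the two reperfusion treatments cannot have under the stated inputs. If it is left as it stands, a null result for either treatment on one-year recurrence could be read as coming from a study with 80% power to detect HR 1.7.

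**Working it through.** **Inputs.** From section 4: HR 1.7, variance 0.36, rho² 0.3, event probability 0.11, power 80%, alpha 5%, N = 997. The section does not say whether the test is one- or two-sided; two-sided reproduces its figure. Exposure prevalences are not in the article and are assumed below.

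**Formula** (Cox regression with a general covariate, Hsieh–Lavori):

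- Events D = (z₀.₉₇₅ + z₀.₈₀)² / [variance × (1 − rho²) × (ln HR)²]
- Patients N = D / event probability
- Power = Φ( √[N × event probability × (1 − rho²) × variance] × ln HR − 1.960 )

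**Step 1: reproduce the stated figure.** (1.960 + 0.842)² gives 7.849 with unrounded quantiles. ln 1.7 = 0.5306, and its square is 0.2816.

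- D = 7.849 / (0.36 × 0.7 × 0.2816) = 110.6 events
- N = 110.6 / 0.11 = 1006, which is 0.9% above 997; an event rate of 11.1% gives 997
- Power at N = 997 with 11% events is 79.7%

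Other readings do not give 997:

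- one-sided test: about 792
- 0.36 taken as a standard deviation: 2794
- 0.36 taken as a prevalence (variance 0.36 × 0.64 = 0.2304): 1572
- rho, not rho², equal to 0.3: 774
- rho² ignored: 704

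So 0.36 entered the calculation as the covariate variance, and the calculation is sound for a covariate that has that variance.

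**Step 2: a 0/1 exposure, best case.** With p = 0.5 the variance is 0.25.

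- D = 7.849 / (0.25 × 0.7 × 0.2816) = 159.3, so 160 events
- N = 159.3 / 0.11, about 1449 (1449 / 997 = 1.45, so 45% more than stated)
- Power at 997 = Φ( √[997 × 0.11 × 0.7 × 0.25] × 0.5306 − 1.960 ) = Φ(4.381 × 0.5306 − 1.960) = Φ(0.365) = 64%
- Detectable HR with 80% power = exp(2.802 / 4.381) = 1.90

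With 900 patients, the lower end of expected recruitment, the best case is 60%.

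**Step 3: range of assumed prevalences** (one-year recurrence, HR 1.7, rho² 0.3, 11% events, two-sided 5%).

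| Prevalence (assumed) | Variance p(1−p) | N needed for 80% | Power at 997 | HR detectable with 80% at 997 |
|---|---|---|---|---|
| 50% | 0.25 | 1449 | 64% | 1.90 |
| 30% | 0.21 | 1724 | 57% | 2.01 |
| 20% | 0.16 | 2263 | 46% | 2.22 |
| 10% | 0.09 | 4023 | 29% | 2.90 |

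**Step 4: can another coding or rho² restore 80%?**

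- With −1/+1 coding the variance is 4p(1−p), which equals 0.36 at p = 10%. But HR 1.7 per unit then means 1.7² = 2.89 between treated and untreated, which is essentially the 10% row of the table.
- With rho² = 0 and p = 50%, N is 1014 and power at 997 is 79%. This abandons the stated rho² of 0.3. At 20% prevalence, power with rho² = 0 is still only 60%.

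**The case against.** The strongest reply is that section 4 never says its covariate is a treatment, or that it is binary. A standard deviation of 0.6 is admissible for a continuous or multi-level covariate. The study plans to measure cytokines, adipokines and metabolomics, and section 3 plans Cox models for determinants in general. This stands. A reader might infer that the article claims 80% power for thrombolysis and thrombectomy and is refuted by its own figures. It makes no such explicit claim, so the point is that its one power figure cannot be carried over to them.

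Four further limits also stand:

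- **The arithmetic is not wrong.** 997 follows from its inputs to within rounding of the event rate.
- **Not every primary exposure is necessarily yes/no.** Drug treatment, comorbidity and complications could be coded as counts or scores, and the article does not say. The claim is firm only for thrombolysis and mechanical thrombectomy.
- **The endpoint is one-year recurrence.** Section 1.1 ties the treatments to stroke-related survival. A reader might take 64% as the maximum power for that outcome too; without a death rate, the article supports no figure.
- **64% is conditional.** It carries over the rho² of 0.3 that was set for the unnamed covariate. With rho² = 0 and exactly half the patients exposed, power is 79%. The figures below 50% rest wholly on assumed prevalences.

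It can also be said that a condensed article may leave the covariate's identity to the full protocol. That would excuse silence on the name. It does not make the printed variance usable for the treatments that head the primary aim, and the article offers no other power figure for them.

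**Conclusion.** The point holds as a mismatch between a sample size assumption and the primary exposures. Under the stated inputs, no prevalence of thrombolysis or mechanical thrombectomy gives 80% power at HR 1.7 with 997 patients. That conclusion needs no assumed prevalence, because the bound of 0.25 is mathematical. It does rest on 0/1 coding, a two-sided 5% test, 11% one-year recurrence and rho² = 0.3 for these treatments. The size of the shortfall below the best case depends on prevalences that the article does not give. Section 16's counterpart in the text, the Discussion, expects loss to follow-up, and the 997 contains no visible allowance for it, so the figures above are if anything favourable.

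Severity is should-fix. Enrolment, data collection and analysis are unaffected; what changes is how a null treatment result on recurrence may be read.

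**What to change.** Keep about 1000 patients and revise section 4 in two places.

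1. Name the covariate and the scale to which the variance of 0.36 and HR 1.7 per unit belong, and say that the 80% applies to that covariate only.
2. For thrombolysis and mechanical thrombectomy, replace 0.36 with p(1−p) at the expected prevalence. State the power at HR 1.7 and the HR detectable with 80% power, for one-year recurrence. If the prevalence is uncertain, two or three values are enough.

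The cost is the rewording of one section and a less favourable stated power. No extra patients are needed.

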## 5. Ethics and Dissemination

The study protocol was approved by the Ethics Committee of the Ludwig-Maximilians-Universität München (date of approval: 29.08.2018, Reference number: 18-196). The study is performed according to the Declaration of Helsinki. Written informed consent is obtained from each study participant. Patients who do not consent or are unable to consent are not be included, except for those for which we obtain consent by the legal caregivers.

## 6. Discussion

In this manuscript, the protocol for a long-term prospective observational cohort study, including patients with acute stroke treated in a hospital, is presented. In this study, the factors associated with the long-term course of this patient group will be investigated. At baseline, data on comorbidities, lifestyle factors, invasive and non-invasive diagnostic and treatment procedures as well as complications during a hospital stay is collected by a personal interview and a chart review. Three and twelve months after hospital discharge, follow-up data will be gathered via postal questionnaires. Furthermore, cause-specific mortality will be assessed through regular mortality follow-up.

Strengths of the present study are the large sample size, the generation of a considerable amount of data, in particular outcome data, and the long-term aspect of the study. Furthermore, data on the occurrence of the acute event are gathered through a face-to-face interview with the patients. Finally, from the study participants, blood is collected and stored. However, the study also has limitations. It is possible that selection bias will occur because patients who are more ill may refuse participation in the study. The present study is designed as a single-center and not as a multicenter study. Finally, another limitation is expected to be a loss to follow-up and the occurrence of missing data.

Altogether, the SCHANA study will add to the current knowledge on the long-term course of stroke and its subtypes. Through this study, prognostic factors regarding different outcomes will be examined. Due to the availability of blood specimens, novel biomarkers which may be associated with the disease course can be identified. Therefore, the results of the study might help guide the various disciplines involved in treating patients with stroke.

